### Nested qualitative evaluation

We will invite a subsample of trial participants to participate in individual semistructured interviews and use maximum variation sampling to ensure a spread of participants differing in age, gender, socioeconomic background and type of phobia. We will obtain written consent (and assent where appropriate) to interview a sample of (1) children receiving OST, (2) their parents/guardians and (3) practitioners delivering OST across all study sites. With parental consent we will recruit and interview parents and children separately. Joint parent–child interviews will be included where participants prefer. The final sample size for the interviews in each participant group will be determined by data saturation, that is, the point where no new themes, ideas and/or concepts emerge. Based on a previous nested qualitative evaluation of patient acceptability of brief psychological interventions,^60^ we estimate that we will need to complete a maximum of 30 interviews with parents, 25 with children and 15 with practitioners.

Interviews with children and their parents will be conducted after participants have completed the final outcome measures at the 6-month follow-up point. Interviews for parents will focus on phobia experiences, personal and family impact, perceived treatment need, treatment expectations and treatment acceptability (eg, content, delivery mode, format, setting and facilitation). Child interviews will focus on the same topics, adapted for age and developmental maturity. Face-to-face interviews with children will draw on the principles of ‘draw and write’ techniques, whereby children will be offered an opportunity to draw a picture relating to their experiences as a prompt to initiate more in-depth discussion.^61 62^ Child interviews will last a maximum of 30 min and parent interviews a maximum of 60 min, with total time guided by the interviewees. Clinician interviews will last for a maximum of 60 min and focus on their experiences and views of delivering OST, the individual and organisational support required and the perceived suitability OST for their patient group.

Interviews with parents and older children (13 years plus) will be conducted face to face in treatment settings or at participants’ homes or via the telephone, depending on participant preference. Interviews with younger children (12 years and under) will be conducted face to face in treatment settings or at participants’ homes, depending on participant preference. Practitioner interviews will take place face to face in their workplace or over the telephone once their own involvement in the trial is complete.

All interviews will be digitally recorded and transcribed verbatim. Analysis will follow a qualitative framework approach,^63^ a widely used method of analysing primary qualitative data pertaining to healthcare practices with policy relevance.^64^ Framework analysis permits both deductive and inductive coding, enabling potentially important themes or concepts that have been identified a priori to be combined with additional themes emerging de novo.

Data coding will be undertaken independently by two trained researchers. We will additionally train a patient and public involvement (PPI) representative to code alongside these researchers to ensure coding takes account of potential differences in perspective. Coders will meet regularly to develop a shared coding manual and to ensure that all emerging codes remain grounded in original data. An Excel spread sheet will be developed which will incorporate preliminary framework themes as column headings and the demographic information related to participants who provided data under each theme. As the constant comparison of new data occurs and the coding team’s understandings of the themes under consideration develop, the framework will be amended and reshaped to enable the introduction of new codes and/or the deletion of redundant, similar or otherwise compromised codes. In this way, a final framework will be achieved that is considered representative of the entire dataset. We will code data from each stakeholder group (children, parents/guardians and practitioners) separately before comparing and contrasting data findings across groups. The final coding manuals for each participant group will be presented with example entries, to the project’s advisory committees to confirm validity, coherence and conceptual relevance.

## Public and patient involvement

The research protocol was developed in partnership with service user groups and was reviewed in terms of both feasibility and relevance. In addition to this, the views of relevant charitable organisations were sought and a representative from the Triumph Over Phobia UK support group is a coapplicant on this application. We have consulted with PPI representatives about their views on the full research proposal and how best to involve patients throughout the proposed project. In particular, we have discussed comments after the first round application with representatives of Triumph Over Phobia. This includes issues around the non-inferiority design, how to measure fidelity and contamination. We have also engaged the York Youth Council, who have commented on this application and discussed the methodology of the trial and the potential impact of the therapy on the community. We see PPI as central to our research. A representative from Triumph Over Phobia is on our trial management group (TMG) and actively involved in the planning and delivery of this research. Applicants KL and PB are named applicants (PI and Co-PI, respectively) on a National Institute for Health Research (NIHR)-funded programme grant seeking to improve user involvement in mental healthcare planning. This programme has been recognised by the former Mental Health Research Network (MHRN) for exemplary carer involvement. Applicant PB has substantial experience of training users and carers in research methodologies, interviewing skills and qualitative data analysis. We recognise the need for independent qualitative data analysis, and will train a service user researcher. The service user representative will be reimbursed for their time, commensurate with current INVOLVE guidelines.

## Ethics and dissemination

### Obtaining informed consent from participants

As all participants in this study are aged 16 or under, consent is required from both a person with parental responsibility, and the participant themselves if they are deemed competent to do so. Where a child is not deemed competent to give full informed consent, we take parental consent and seek assent from the child. Prior to the consent meeting, the parents and the children receive information about the study and have the opportunity to discuss any questions or concerns with members of the research team. Two age-specific versions of the child information sheets are available: one for those aged 7–11 years and one for those aged 12–16 years. All information leaflets and consent forms are codeveloped by the research team and PPI representatives to ensure acceptability among participants. If a participant wishes to withdraw from their allocated intervention, we check whether they are still agreeable to participate in the planned follow-up assessment at 6 months, so that their outcomes can be included within our ITT analysis.

### Data management

Trial data are extracted from source documents and entered onto the CTRU’s in-house data management system (Prospect). Prospect stores data in a PostgreSQL database hosted by the University of Sheffield. The database uses industry standard techniques to provide security, including password authentication and encryption using Secure Sockets Layer (SSL) /Transport Layer Security (TLS). Access to Prospect is controlled by user names and encrypted passwords. A comprehensive privilege management feature ensures only the minimum amount of data required is available to each individual to complete their tasks. The system has a full electronic audit trail and is regularly backed up. Access to data is restricted to users with appropriate privileges only. All data are collected and retained in accordance with the Data Protection Act 1998 and Sheffield CTRU standard operating procedures (SOPs).

### Research governance and conduct of the trial

Trial monitoring procedures and site monitoring are undertaken at a level appropriate to a risk assessment performed by the Trial Sponsor (Leeds and York Partnership NHS Foundation Trust, [name]) and the Sheffield CTRU. Three committees govern the conduct of this study, in accordance with Sheffield CTRU’s SOPs: a trial steering committee (TSC), an independent data monitoring and ethics committee (DMEC) and a TMG.

The TSC consists of an independent chair, an independent subject specialist, an independent clinical academic, an independent statistician and a patient representative. The TSC meets approximately every 6 months from the start of the trial. The DMEC consists of an independent chair, an independent statistician and an independent ethics specialist experienced in research with children and families. The TMG comprises the coapplicants and the two trial managers who are jointly supervised by the Chief Investogator (CI), the director of the Sheffield CTRU and a lead trial manager in the CTRU. Meeting attendance of the coapplicants depends on each meeting’s agenda and relevance to their role.

### Adverse events

An adverse event monitoring form is used to record any untoward occurrence affecting the participant after each therapy session by the therapist and at follow-up by the research assistant. Such an event can be directly related, possibly related or unrelated to the intervention. An occurrence is recorded if it is suspected to be related to the intervention or an aspect of the research procedures; the therapist assesses relatedness and research assistants seek advice from the site principal investigator. The occurrence of adverse events during the trial is monitored by the trial oversight and management groups, particularly the DMEC and the TSC. All adverse events are assessed for seriousness, and will be recorded as a serious adverse event) if they are life threatening, or require hospitalisation or prolongation of existing inpatient stay, or result in persistent or significant disability or incapacity or death.

No pharmaceutical compounds or medical devices are used in this trial, therefore, clinical trials authorisation is not required.

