### Interventions

#### One-session treatment

OST is a variant of CBT, but rather than being delivered in weekly 45–60 min sessions as in conventional CBT, OST is delivered in a longer single session (approximately 3 hours). Prior to the single session, a 1-hour assessment/planning session takes place during which the practitioner carries out an assessment in order to plan the treatment session. This involves:Determining the nature, history and associations of the phobia.Determining any maintaining factors for the phobia (eg, what the child avoids, what safety behaviours she/he engages in, how friends and family may collude with the phobia).Collecting information about the child’s cognitions including catastrophic thoughts (eg, what do you think may happen if…, what goes through your mind when you…).Generating a fear hierarchy (ie, a ‘ladder’ of situations or objects that the child avoids because of their phobia, in the order of the fear or anxiety evoked, starting from the least frightening).Explaining what is involved in treatment and that the exposure tasks are graded and negotiated in every step of the way and that nothing will ever happen without the child’s permission.

The single session combines graded exposure, participant modelling, reinforcement and cognitive challenges. The main principle of graded exposure is that the child gradually confronts the situations from their fear hierarchy and remains in each situation until their anxiety/fear subsides at least by 50%. In participant modelling, the therapist first demonstrates to the child how to interact with the phobic object and then helps the child gradually approach the phobic object by joint approaches with the therapist gradually fading involvement. Reinforcement from the therapist may take the form of social praise, encouragement. Finally, the therapist uses the exposure tasks as means for actively eliciting, challenging and testing negative cognitions or catastrophic thoughts associated with the feared situation and by promoting positive cognitions in phobic situations. It is important that the child maximises, maintains and generalises their gains from graded exposure by practising self-directed and parent/carer supported exposure tasks at home for the ensuing weeks. Maintenance tasks include a commitment to refrain from avoiding or escaping from feared situations and to deliberately engineer or enter a feared situation regularly.

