#### Cognitive–behavioural therapy

CBT helps people to change unhelpful beliefs and behaviours arising in feared situations, such as catastrophic thinking and safety behaviours. Interventions based on CBT are the dominant model of treatment for specific phobias, and are supported by a robust literature attesting to its efficacy.^8–12^ CBT interventions are often delivered in 45–60 min sessions every week or fortnight over several weeks or months. Each CBT session takes the form of structured discussions with a therapist, has a specific agenda and sets homework tasks for the child or young person between sessions. CBT for children and young people with specific phobias aims to help the child/young person to: (1) recognise anxious feelings and bodily reactions to anxiety; (2) gradually confront their feared situations until their anxiety subsides; (3) capture and challenge anxious thoughts when faced with a phobic situation or object; (4) challenge avoidance behaviours, or behaviours that maintain or reinforce the phobia and (5) develop coping strategies and anxiety management techniques if distress and physical responses to anxiety are overwhelming. There is no recommended number of CBT sessions for specific phobias but it can vary between 4 and 20 sessions.

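### The adverse-event section gives two conflicting recording scopes, and session-linked forms make the number of recording occasions differ by arm

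*Protocol article*

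**What the plan says.** Three consecutive sentences of the Adverse events section set the rule. The first gives scope and timing: "An adverse event monitoring form is used to record any untoward occurrence affecting the participant after each therapy session by the therapist". The same sentence has a research assistant complete the form when the child is followed up. The second lists the categories: "Such an event can be directly related, possibly related or unrelated to the intervention". The third sets a condition: "An occurrence is recorded if it is suspected to be related to the intervention or an aspect of the research procedures". It goes on to say who decides: "the therapist assesses relatedness and research assistants seek advice from the site principal investigator". The section then has all adverse events assessed for seriousness, and it gives monitoring to the oversight and management groups, particularly the DMEC and TSC.

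The number of sessions comes from the Interventions section. For OST, "Prior to the single session, a 1-hour assessment/planning session takes place", followed by one treatment session of about 3 hours. For CBT, "There is no recommended number of CBT sessions for specific phobias but it can vary between 4 and 20 sessions".

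**The concern.** Two separate problems meet in one short section.

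- **Scope.** If an event must be suspected to be related before it is recorded, the unrelated category has almost no use. Two sites could each follow the text in good faith and collect different data. On the narrower reading, relatedness acts as an entry filter instead of a classification. For session forms the filter is applied by someone who knows the arm. An event left off the form may miss the seriousness assessment and the committees, and no later analysis plan can recover it.
- **Timing.** Therapist forms follow sessions, and the number of sessions is the very thing that differs between the arms. Counts pooled over all forms would partly reflect how often therapists had a form to fill in. After the OST treatment session the section names no further form until follow-up, although home exposure practice continues for weeks.

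What is at stake is the reading of the safety data by the DMEC and TSC, and later by readers weighing a brief intensive treatment against a longer one. The primary analysis is not affected.

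**Working it through.** **Scope.** The section states no figure to reproduce, so the sentences are set side by side.

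1. Sentence 1 covers every untoward event, with no condition on cause.
2. Sentence 2 allows for events unrelated to the intervention.
3. Sentence 3 makes suspected relatedness to the intervention or to research procedures the condition for recording.

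Sentences 1 and 2 imply recording first and classifying second. Sentence 3 reverses the order. The category in sentence 2 could then hold only events tied to research procedures, or events suspected at first and reclassified later.

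Who applies the filter: on session forms, the therapist, who delivers the allocated treatment. The Blinding section covers research assistants, statisticians and health economists, not therapists. At follow-up it is the research assistant, who is not told the allocation, with advice from the site principal investigator. The condition in sentence 3 is not limited to therapists, so on the narrower reading the 6-month form is filtered as well.

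**Recording occasions per participant.** Inputs:

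- OST: 1 planning session + 1 treatment session = 2 (One-session treatment; the per-protocol definition under Data analysis names the same two).
- CBT: 4 to 20 sessions (Cognitive–behavioural therapy; the per-protocol minimum is 4).
- Follow-up form: 1 in each arm (Adverse events).

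Ratio = (CBT sessions + shared form) / (OST sessions + shared form).

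| Occasions counted | OST | CBT | Ratio |
|---|---|---|---|
| Therapist forms only | 2 | 4 to 20 | 4/2 = 2.0 to 20/2 = 10.0 |
| Therapist forms plus 6-month form | 3 | 5 to 21 | 5/3 = 1.67 to 21/3 = 7.0 |
| As above, planning session not counted as therapy | 2 | 5 to 21 | 5/2 = 2.5 to 21/2 = 10.5 |

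The second row is the main result, because it counts every occasion that the section names and both OST sessions.

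**From occasions to recorded events.** As an illustration only, assume that each form has the same independent chance p of carrying a record. The documents give no such figure, so p is varied from 1% to 10%. The probability of at least one record over k forms is 1 − (1 − p)^k.

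| p | OST, k = 3 | CBT, k = 5 | Ratio | CBT, k = 21 | Ratio |
|---|---|---|---|---|---|
| 0.01 | 0.030 | 0.049 | 1.65 | 0.190 | 6.41 |
| 0.10 | 0.271 | 0.410 | 1.51 | 0.891 | 3.29 |

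Even under this assumption, the ratio of participants with any recorded event falls short of the ratio of forms.

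**The case against.** The strongest reply is that this is loose wording in an article that condenses a fuller protocol and relies on operating procedures that are not shown. Sentence 3 does not say that only related events are recorded. A reader might infer that unrelated events never enter the database; the text does not go that far. Hospital stays, urgent care and A&E visits are also collected from parents in both arms by the Resource Utilisation Questionnaire, with no relatedness filter. Targeted recording could be a deliberate choice in a trial without a medicinal product or device. These points soften the consequence. They do not remove the conflict, which is printed in consecutive sentences, and the questionnaire is not adverse-event reporting.

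On timing, a reader might infer that CBT has 2 to 10 times as many chances to record harm. That counts therapist forms only and leaves out the 6-month form that both arms share. The upper end also needs 20 sessions, and the article gives 4 to 20 as a general range, not as this trial's expectation.

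Nor do more forms mean proportionally more recorded events. If each form covers the time since the last contact, which is not stated, capture need not scale with the number of forms. Events arising from extra sessions are real exposure to a longer therapy. At the lower end, contact time is similar: 1 + about 3 = about 4 hours in OST, against 4 × 45–60 minutes = 3 to 4 hours in CBT.

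The gap before follow-up is not peculiar to OST either. CBT sets homework and also has no named form between its last session and 6 months. All of this stands, and it limits the point to ascertainment in pooled counts.

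**Conclusion.** The point holds in two parts. First, the recording scope is stated inconsistently. If the narrower sentence is followed, judgement made with knowledge of the arm would partly decide which session-form events exist in the data. Second, recording occasions differ by design: 3 in OST against 5 to 21 in CBT, a ratio of 1.67 to 7.0. This assumes a form after both OST sessions, attendance within the stated CBT range and one follow-up form each. Pooled counts are therefore open to differential ascertainment, probably towards more recorded events in CBT. How much of any excess would be ascertainment and how much genuine exposure cannot be told from the documents.

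A reader might go further and conclude that safety cannot be compared between the arms, or that OST will look safer merely because it is asked about less often. The documents do not support this. The 6-month form is on a common schedule and is completed by an assessor not told the allocation. The article plans no formal between-arm test of adverse events; it speaks of monitoring. That form is a sound basis for comparison once the scope conflict is settled. The correction is worth making because it is cheap and because unrecorded events cannot be recovered later.

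**What to change.** 1. Reconcile the two sentences so that untoward events are recorded irrespective of suspected relatedness, with relatedness and seriousness classified afterwards. Apply the same rule to the therapist form and the follow-up form.
2. Base any between-arm safety summary on the 6-month form, with the same recall period in both arms and completed by the research assistant not told the allocation.
3. Report events from session forms separately by arm, as description, with the number of sessions alongside.

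This needs form guidance and reporting wording only. It uses forms that already exist and leaves treatment and the visit schedule unchanged. The downside is that some unrelated minor events must be logged.

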### Dissemination of the research findings

We will publish the study’s findings in peer-reviewed academic journals and present at local, national and international conferences where possible. Furthermore, we will publish a short summary of the results on the ASPECT study website that can be accessed by all trial participants as well as relevant interest groups, including patient groups. Finally, towards the end of the trial, our PPI representatives will organise a meeting with stakeholders including parents and professionals working with young people with anxiety disorders to specifically discuss the dissemination of the study findings and put together a dissemination plan.

### Trial status

Protocol V.3, 24/04/17. Recruitment to the trial began in June 2017 and is estimated to be completed in July 2019, with the final follow-up assessments completed in March 2020.
